### 2.4. Analyses

#### 2.4.1. Quantitative Analysis

Prior to data collection, we estimated that 107 subjects for each cohort was needed (d = 0.5, SD = 1.0, α = 0.05, power 80%) in order to detect a statistical difference between our control (i.e., T_0_) and intervention groups (i.e., T_1_ and T_2_). Assuming each class consisted of a minimum of 25 students, five schools were required. When we took into account the cluster design and possible non-response, we took a sample that consisted of twice the number of schools needed [44]; hence, the sample size was ten primary schools.

We will conduct a series of multilevel regression analyses. This analysis takes into account different clusters (i.e., class level, potentially school level). Same-age data from different time points and cohorts will be compared, in which cohorts consist of a group of children from the same age from all ten participating schools. We will create a variable for at-school consumption by combining the food and drinks consumed in the first and second school break, i.e., sugar-sweetened beverages, water or tea without sugar, milk, whole wheat bread, fruit, vegetables, snacks consumed at school. This will be done based on the parent and child questionnaires, and the photographs. Behavioural determinants (attitude, knowledge, social norm, modelling, physical environment, liking and habit formation) will be derived from the parent and child questionnaires.

To analyse the effect of the intervention on the combined scores of at-school dietary behaviour and behavioural determinants, we will use multilevel regression analyses. For continuous outcome variables we will use linear multilevel regression models with time point as first level variable and grade as second level variable. When variables are not normally distributed, we will use Poisson multilevel analysis. For categorical variables we will use logistic multilevel models. To examine whether observations cluster at school level, we will add schools as third level in the linear models. If this is the case, schools will be added to all models—creating a three-level structure—and for categorical variables we will shift to a GEE analysis.

To explore the moderation effects by SEP, age in years, sex and ethnicity, we will add interaction terms to the model. When these terms are significant, we will stratify the analyses for these specific subgroups.

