Finally, to study whether children compensate for at-school dietary changes when they are home, we will adjust at-school child dietary behaviour for at-home child dietary behaviour (i.e., combined score of consumption in the morning and after school, derived from the parent and child questionnaire). A significance level of *p* = 0.05 will be used and *p* = 0.10 for moderation effects. For the analyses we will use IBM SPSS Statistics Version 21.0 (IBM, Armonk, NY, USA) and STATA/IC 15.1 (StataCorp LLC., College Station, TX, USA).

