A limitation of the ESC design is the difference in the time points of data collection of control and intervention groups, since baseline measurements represent the control and the follow-up measurements represent the intervention groups. Therefore, the design does not allow to control for general societal time trends that coincide with the intervention, such as a new supermarket next to the school. To mitigate this limitation, we conduct an extensive process evaluation.

This evaluation study is set up in a complex real-life setting, which may influence how the intervention is delivered [27]. Contextual factors to consider are: the wide dissemination among primary schools in Amsterdam, the support of a team of health promotion professionals, and the embedding in health promotion programmes and Amsterdam’s municipality (i.e., ensuring structural, financial and political support and connections with other health promotion interventions in Amsterdam) [17]. These factors might influence the implementation and, thereby, the outcomes.

To get a grip on the complexity of the setting, we include a process evaluation. Process measures can be used to explain differences in effectiveness between clusters (e.g., schools), and understand how and under which conditions an intervention is effective [27,28].

Accurate measurement of dietary behaviour, especially in children, is challenging. In general, the validity of self-report is questionable, because children have a short attention span [35] and outcomes can be biased due to recall and social desirability [46,47,48,49]. For instance, children tend to overestimate their fruit and vegetable intake in self-reported dietary methods [50,51].

Another common challenge is to motivate people to participate and repeatedly fill out long questionnaires. In our study, data collection relied on a number of stakeholders to motivate children and parents to participate; we needed the help of the health promotion professional to contact primary schools, the school principal and Jump-in coordinator to approve study participation; lastly, the teachers to motivate children and parents to fill in questionnaires and allow us to photograph the food and drinks that children bring to school. Even though we incorporated strategies to optimise participation in this study (e.g., tailoring recruitment procedures to the schools’ needs), this remains challenging.

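### The models give ten schools at most a random intercept, or a GEE with no stated few-cluster correction, although the before-after contrast depends on how much change varies between schools

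*Protocol article*

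**What the plan says.** Section 2.4.1 names class as the clustering level and school only as a possible one. The linear models have time point as the first level and grade as the second. School is then tried: "To examine whether observations cluster at school level, we will add schools as third level in the linear models". No criterion for deciding is given. If clustering is seen, school goes into all models as a third level, and "for categorical variables we will shift to a GEE analysis". The cluster unit, the variance estimator and any small-sample correction for the GEE are not stated, and no term lets the time effect differ between schools. On error rates: "A significance level of *p* = 0.05 will be used and *p* = 0.10 for moderation effects". On the number of clusters: "hence, the sample size was ten primary schools".

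Other sections treat school as the place where effects may differ. Box 1 describes a plan tailored to each school. Section 2.1.4 measures dose delivered by how many of the five policy components were implemented, and expects context to help interpret possible outcome differences between schools. Section 3 says "Process measures can be used to explain differences in effectiveness between clusters (e.g., schools"). It also gives a new supermarket next to a school as an example of a time trend that the design cannot control.

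**The concern.** Baseline measurements are the control and follow-up measurements are the intervention, in the same ten schools. A stable difference between schools therefore cancels from the comparison. What remains is the variation between schools in how much they changed. A school intercept does not carry that variation. If it is present and has no term of its own, the model treats many classes as independent evidence on change when there are only ten independent units.

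GEE clustered on school does capture this variation in its robust variance. That variance is estimated from ten clusters, however, and the usual z-test is too liberal with so few. At stake are the p-values and confidence intervals for the main at-school dietary outcomes.

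**Working it through.** **The plan's own figures.** The plan computes no error rate; the reference is its nominal 5%, taken as two-sided. Its only derived figure is the sample size ("we estimated that 107 subjects for each cohort was needed"). The stated inputs give 2 × (1.96 + 0.84)² / 0.5² ≈ 63 per group, not 107, but that is a separate matter. Used here are ten schools and 25 children per class ("Assuming each class consisted of a minimum of 25 students, five schools were required"; 107 / 25 = 4.28, rounded up to 5).

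**Assumed inputs (not in the document).** Shares of total variance: school 0.02, class-year 0.02, school-by-time *v* from 0 to 0.03, remainder *e* = 0.96 − *v*. One baseline and one follow-up wave; children independent given their class.

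**Linear models, four grades pooled (40 classes per wave).** Write *c* = 0.02 + *e*/25 for the variance of a class mean apart from *v*.

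- True variance of the contrast: 2 × (*v*/10 + *c*/40).
- Variance reported with a school intercept only: 2 × (*c* + *v* × 4 × 9/69) / 40. The 69 is the within-school degrees of freedom, 80 − 10 − 1, of which 9 carry the school-by-time variation.
- Type I error: the two-sided normal tail beyond 1.96 / √(true/reported).

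| *v* | true | reported | SE understated by | type I error, formula | type I error, 20,000 simulated trials |
|---|---|---|---|---|---|
| 0 | 0.00292 | 0.00292 | 1.00 | 5.0% | 5.3% |
| 0.01 | 0.00490 | 0.00316 | 1.25 | 11.5% | 11.5% |
| 0.02 | 0.00688 | 0.00340 | 1.42 | 16.8% | 17.0% |
| 0.03 | 0.00886 | 0.00364 | 1.56 | 20.9% | 21.6% |

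Across the school variances tried (0 to 0.05), the simulated ranges are 11.5-12.0%, 16.6-17.2% and 20.9-21.6% for *v* = 0.01, 0.02 and 0.03.

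**How the result depends on the set-up.**

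- *Single grade.* With one class per school and wave, the class-year term absorbs most of the school-by-time variation. Simulated error is 6-8%.
- *Eight grades pooled.* Section 2.3.1 has lunchboxes photographed in all grades. Simulated error is 12-34% for *v* from 0.005 to 0.03.
- *Level-two unit persisting over years.* If this unit is a school-grade and not a class-year, four grades give 17%, 27% and 34% at *v* = 0.01, 0.02 and 0.03 with no class-year variance. The text does not settle which unit is meant.

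**Conditional entry of school.** With four grades, school variance 0.02 to 0.05 and *v* = 0, the two-level model rejects in 1-3% of trials. The procedure that first checks for school clustering rejects in about 5.2%. Conditional entry is not a source of inflation.

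**GEE clustered on ten schools.** In the balanced linear case the uncorrected robust z statistic is a *t* on 9 df divided by √0.9.

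- Uncorrected: P(|t₉| > 1.96 × √0.9 = 1.859) = 9.6%.
- Variance scaled by 10/9, still compared with 1.96: P(|t₉| > 1.96) = 8.2%.
- Simulated logistic GEE, exchangeable, 500 runs per setting, with assumed logit-scale school SD 0.4, class-year SD 0.25 and school-by-time variance 0 or 0.1: 10.8%, 12.2% and 13.6%. Monte Carlo error is about 1.4 points (√(0.108 × 0.892/500) = 0.014).

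The problem does not need school-by-time variance; it comes from having ten clusters.

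**After correction.** A school-by-time analysis with *t* on 9 df rejects in 4.7-5.3% of trials in every linear setting. For the logistic GEE, scaling the variance up by 10/9 and using *t* on 9 df gives 5.2%, 7.2% and 7.0%.

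**The case against.** The document gives no intraclass correlation and no school-by-time variance, so the linear figures rest on assumptions. At zero variance nothing is wrong. The article sizes the study per cohort and compares same-age cohorts; if each grade is analysed separately, the inflation is modest. Silence about a random slope or a small-sample correction is not a refusal to use one, and a fuller analysis plan could supply both. No outcome is named as categorical, and non-normal variables go to Poisson multilevel models, so it is unclear how many main outcomes would reach GEE. All of this stands, and it makes the conclusion conditional.

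Three stronger readings are tempting but unsupported:

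- *Checking for school clustering first inflates error.* It does not for this contrast, because the school intercept cancels; the procedure runs at about 5.2%.
- *GEE is wrong because it takes one cluster level or gives a population-average odds ratio.* Clustering on school, the top level, covers the classes nested in it and allows for school-specific change. A population-average odds ratio is a legitimate target for a city-wide programme.
- *Error rates exceed 5% whatever happens.* The article fixes neither the variance components nor the GEE variance estimator, so this cannot be said.

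The objection does not remove the structure that the article commits to. School is optional and appears only as a level, and the method for categorical outcomes depends on what the linear outcomes show. Yet the article's own account of tailored implementation and differing effectiveness makes zero school-by-time variance an optimistic assumption.

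**Conclusion.** The concern holds conditionally. If change differs between schools, the linear models as described understate the standard error: about 12-21% type I error for school-by-time variance of 1-3% with four grades pooled, about 6-8% with a single grade, and about 5% at zero variance. If GEE is clustered on the ten schools with an uncorrected robust z-test, type I error is about 8-14% whatever the school-by-time variance.

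The linear figures rest on assumed variances and on pooling grades. The GEE figures rest on school being the cluster unit, which the sentence implies but does not state, and on no correction being applied. Because the article describes these analyses as still to be done, the point is worth acting on as a change of wording.

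**What to change.** - Include school in every model as a design level, with no data-dependent step.
- Add a random school-by-time-point effect to the linear and Poisson multilevel models, and base inference on the time contrast on about 9 df.
- For categorical outcomes, choose one method in advance, independently of the linear results. Either use GEE clustered on school with a bias-corrected variance and *t* on 9 df, or a mixed logistic model with a school-by-time effect and comparable small-sample inference. Changing to a mixed logistic model with z-tests would not by itself solve the ten-cluster problem.

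The cost is analysis wording and wider intervals. Using *t* on 9 df multiplies the width by 2.262/1.96 = 1.15 even at zero school-by-time variance; at *v* = 0.01 with four grades the total is about 1.25 × 1.15 = 1.44. In the linear simulations, power at the planned d = 0.5 stays at 0.92-0.98 with one grade and at least 0.997 with four. For d = 0.2 with four grades it is 0.47-0.90, depending on the school-by-time variance.

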## 1. Introduction

Childhood overweight and obesity are leading health concerns with a prevalence of 18 per cent of children 5 to 19 years old worldwide [1]. Although childhood overweight rates appear to stabilize in some high-income countries [2], overweight rates are still significantly higher and rising in lower socio-economic and migrant groups [3,4]. Childhood obesity increases the risk of early-onset physical health issues (e.g., type 2 diabetes, cardiovascular disease and some cancers) [5] as well as social and mental health issues (e.g., depression, being bullied and low self-esteem) [6]. Furthermore, it is likely to track into adulthood [7]. These health inequalities and adverse health outcomes highlight the importance of early targeted childhood obesity prevention.

A healthy diet is one of the key components in the prevention of overweight and obesity [5]. Yet, only about 40 per cent of children in The Netherlands meet daily fruit and vegetable intake recommendations [8] and roughly 90 per cent of Dutch children exceed the WHO’s daily recommendations of sugar intake [9,10] with sugar-sweetened beverages and unhealthy snacks being the biggest contributors [11].

School-based interventions may be promising with regard to stimulating fruit and vegetable intake among children [12]. An example of a school-based intervention that aims to promote children’s healthy dietary behaviour is a lunchbox intervention i.e., an intervention that aims to improve the foods and beverages children consume at school that are generally packed by parents. A recent meta-analysis reported an overview of lunchbox interventions [13] showing that lunchbox interventions increased the provision of vegetables, but the effects on fruit, discretionary foods and sugar-sweetened beverages were unclear. The authors recommend examining moderation of intervention effects by socio-economic position (SEP).

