While dietary behaviour (e.g., drinking sugar-sweetened beverages) tends to be worse among children from ethnic minority groups [4,14] and people with a low SEP benefit more from healthy options in the food environment [15], effective interventions on dietary habits for children with a lower SEP or from an ethnic minority group are lacking [16]. To promote healthy dietary behaviour among children living in disadvantaged neighbourhoods, the Public Health Service of Amsterdam implemented an intervention targeting dietary habits in primary schools in disadvantaged neighbourhoods in Amsterdam [17,18]. In these neighbourhoods, obesity rates tend to be higher [19]. This intervention aims to implement a healthy nutrition school policy, including a healthy lunchbox intervention, and is part of the Jump-in programme that also focuses on promoting physical activity which has been evaluated previously [20,21]. Box 1 presents a detailed description of Jump-in.

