### 2.3. Outcome Measures

#### 2.3.1. Effect Measures

The main outcome was children’s dietary behaviour at school; we examined differences in the consumption of water or tea without sugar, milk, sugar-sweetened beverages, fruits or vegetables, whole wheat bread, and unhealthy snacks. We included a-priori categories as an indicator of children’s dietary behaviour that were targeted by the intervention (i.e., the consumption of water or tea without sugar, milk, sugar-sweetened beverages, fruits or vegetables, whole wheat bread, and unhealthy snacks). Secondary outcome measures included dietary behaviour at home with regard to the products mentioned above and several determinants of dietary behaviour: attitude, knowledge, social norm, modelling, physical environment, liking and habit formation.

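### Stratified subgroup results depend on an interaction reaching p = 0.10, so those shown are selected for large differences, and the plan commits to no SEP-specific estimate when the test misses

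*Protocol article*

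**What the plan says.** Section 2.4.1 of the protocol article fixes the handling of moderation in three steps.

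- Interaction terms: "To explore the moderation effects by SEP, age in years, sex and ethnicity, we will add interaction terms to the model".
- Threshold: "A significance level of *p* = 0.05 will be used and *p* = 0.10 for moderation effects".
- Consequence: "When these terms are significant, we will stratify the analyses for these specific subgroups".

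The four moderators are treated alike. The article states no count of interaction tests and no multiplicity adjustment. It does not say that interaction or subgroup estimates will be shown whatever the p-value, nor that non-significant ones will be withheld.

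The outcomes to which the rule applies include the main ones in 2.3.1: "we examined differences in the consumption of water or tea without sugar, milk, sugar-sweetened beverages, fruits or vegetables, whole wheat bread, and unhealthy snacks". That is six categories. Section 2.4.1 lists fruit and vegetables separately, which makes seven, and adds seven behavioural determinants.

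On the importance of SEP, the Introduction reports that a recent meta-analysis recommended examining moderation by SEP. It also says that "effective interventions on dietary habits for children with a lower SEP or from an ethnic minority group are lacking". Box 1 describes a programme aimed at areas with relatively many low-SEP and ethnic-minority children. The study aim at the end of the Introduction is the effect in children aged 4 to 12 overall.

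**The concern.** Making a subgroup analysis conditional on its own interaction test does harm in both directions.

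When the test fires, the stratified estimates that reach the report are there because the observed difference was large. Across many tests at 0.10 some will fire by chance, and real differences that fire will on average look larger than they are.

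When the test does not fire, the plan commits to no subgroup estimate. For sex or age that matters little. For SEP it matters more, because the article's own case for the study leans on low-SEP and ethnic-minority children. A reader asking what the programme did for low-SEP children should get an estimate with an interval, not one that appears only after a significant test.

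**Working it through.** **The plan's own figure.** The article gives no error rate or power for the moderation rule, so there is none to reproduce. Its one design figure is 107 per cohort. The stated inputs give 2 × (1.960 + 0.842)² / 0.5² = 62.8, that is 63 per group (64 with a t-test). That gap is a separate matter. Because 107 is also the size before the schools were doubled, it is not used below.

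**Inputs from the article.** Four moderators; level 0.10 (taken as two-sided); six main food categories; ten schools; classes of at least 25.

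**Assumptions, not in the article.** Correlations between tests; a comparison of two groups of 250 (10 schools × 25, one class per grade, before non-response); SD 1; low-SEP share 50% or 80%; a design effect of 1.7 where shown.

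**1. Chance of at least one trigger with no moderation**, for one data source and one contrast.

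Independent tests, 1 − 0.9^k:

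| Tests | k | Chance |
|---|---|---|
| SEP only, six outcomes | 6 | 46.9% |
| Three moderators (age dropped) × 6 | 18 | 85.0% |
| Four moderators × 6 | 24 | 92.0% |
| Four moderators × 7 | 28 | 94.8% |

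The 18-test row is shown because age was removed from the questionnaires as of May 2018 (2.2.2). The expected number of false triggers among 24 tests is 24 × 0.10 = 2.4, whatever the correlation.

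Correlated test statistics (simulated, 24 tests):

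| Assumed outcome correlation | Moderators correlated 0.3 | All 24 tests equally correlated at this value |
|---|---|---|
| 0.3 | 87% | 84% |
| 0.5 | 82% | 71% |
| 0.8 | 66% | 40% |

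For SEP alone over six outcomes, correlations of 0.5 and 0.8 give 37% and 25%.

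**2. Chance that a real SEP difference fails to trigger the rule.**

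SE of the interaction = √(2/(np) + 2/(n(1−p))), with n = 250 per group and p the low-SEP share.

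- p = 0.5: √(2/125 + 2/125) = 0.179. For a 0.5 SD difference, 0.5/0.179 − 1.645 = 1.15, power 87.5%, missed 13%.
- p = 0.8: √(2/200 + 2/50) = 0.224. For 0.5 SD, 2.236 − 1.645 = 0.59, power 72.3%, missed 28%.
- For 0.25 SD the same formula gives 60% and 70% missed.
- With a design effect of 1.7 (SE × √1.7), a 0.5 SD difference is missed 31% and 47% of the time.

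**3. Size of what is shown when the rule fires.** The observed difference must exceed 1.645 × SE, that is 0.29 SD (p = 0.5) or 0.37 SD (p = 0.8). If the true difference is zero, the mean absolute difference among triggered results is SE × φ(1.645)/0.05 = 2.06 × SE, that is 0.37 or 0.46 SD. No smaller SEP difference, real or not, can reach the stratified results under these assumptions.

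**The case against.** The strongest reply is that moderation is labelled exploratory. A relaxed 0.10 level followed by stratification is a common convention for that purpose, and a family-wise rate is a yardstick for confirmatory claims. This stands as a limit on how serious the point is. It does not excuse showing estimates selected for size: exploratory results are most useful when shown in full.

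Four stronger readings are tempting, and the article does not support them.

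- *That the low-SEP effect will go unreported.* Only the stratified analysis is conditional. The interaction model is fitted in every case and contains the effect in each group. What can be said is that the plan commits to no SEP-specific estimate when the test misses.
- *That a non-significant interaction will be taken as equal effects.* No sentence says so.
- *That the low-SEP effect is the study's target question.* The stated aim is overall. Low-SEP children are a main part of the programme's target population, and the pooled estimate already draws on schools enrolled in that programme.
- *That 66-92% is the chance of a false SEP finding, or a property of the protocol.* It pools all four moderators. The test count follows from the article's lists but is not stated there, and the lower end rests on assumed correlations.

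On power, someone might use 107 per group and find a 0.5 SD difference missed 43-57% of the time, but that is the size before inflation. If grades 5-8 are pooled (4 × 250 = 1,000 per wave before non-response), even a 0.25 SD difference is missed only 13-28% of the time, or 31-47% with a design effect of 1.7. So low power is possible, especially for small differences, but it is not established for every analysis.

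Finally, the remedy shows more subgroup estimates, not fewer. That is true, but showing all of them removes the selection.

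**Conclusion.** The point holds as a criticism of a stated rule, not of an omission. With 24 or more tests at 0.10 and no moderation, some stratification is likely: 92% under independence, roughly 66-87% at assumed outcome correlations of 0.8-0.3, and down to about 40% if all tests correlate at 0.8. For SEP alone over six outcomes the figure is at most about 47%. In the other direction, a 0.5 SD difference between SEP groups is missed about 13-28% of the time at an assumed 250 per group, more with clustering or a smaller difference.

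The selection effect itself needs none of these assumptions; only its size does. This is an inexpensive improvement to an exploratory analysis, worth making because SEP figures so strongly in the article's rationale. It leaves the main-effect analysis untouched.

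**What to change.** Replace the stratification sentence in 2.4.1 with wording to this effect:

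> SEP is the pre-specified moderator. For every main outcome, the effect in each SEP group and the difference between groups, with 95% confidence intervals, will be reported from the joint interaction model whatever the interaction p-value. Interactions with age, sex and ethnicity are exploratory and will be reported in the same form. Separate stratified models will not be triggered by significance.

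Adding that a non-significant interaction will not be read as equal effects would guard against a misreading that the present text neither makes nor rules out.

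The cost is a wording change and one added table. No new data are needed, because the joint model is already planned, and 2.4.1 describes these analyses in the future tense. The downside is that more estimates, with wider intervals, will be on show.

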To assess children’s dietary behaviour, children, parents and teachers filled in questionnaires and we photographed the food and drinks children brought to school at T_0_, T_1_ and T_2_. The executive researcher and research assistant conducted the measurements with support from health promotion professionals and MSc students. In all grades children’s lunchboxes were photographed. In addition, children in grade 5–8 filled in questionnaires which was aided by the research team when a question was unclear. Data collection followed a few logistical considerations: (1) data collection was conducted before 10 AM (school breaks usually take place at 10 AM), (2) data collection was not conducted on Mondays in grades 5–8 (to avoid that children reported on weekend days), (3) data collection at fruit days was avoided (i.e., Dutch schools can sign up for the EU schoolfruit project in which they receive free fruits/vegetables a few days a week for 20 weeks), and (4) short schooldays were avoided. The children received a questionnaire for their parents in an envelope to take home. A few days before the deadline to hand in the questionnaire, the parents received a reminder to fill in the questionnaire. Prior to the start of Jump-in, health promotion professionals made agreements with schools ensuring the schools’ involvement with the programme and introduced the evaluation study. Subsequently, the coordinating researcher explained in detail what the study entailed including the required time investment. After each data collection wave schools received an incentive and a factsheet illustrating the percentages of drinks and foods consumed by the pupils. Additionally, the existing relationship between the health promotion professional and the school facilitated optimal compliance to the study protocol. Completed parent questionnaires were returned to the school and collected by the teacher. After data collection, the questionnaires were scanned. The food groups depicted on the photographs were entered in a Microsoft Access database by one the researchers. Categorising products to certain food groups and specifying the quantities was done based on an established Dutch Food Composition Database [34]. In the Netherlands, lunch boxes, packages and sipping cups have a standardized size, which gave us an indication of the quantity of the products consumed by children. Beverages are usually offered in 0.21 (e.g., packages of sugar-sweetened beverages), 0.2751 (e.g., sipping cups) or 0.51 (e.g., water bottles) packages. Bread usually has a standardised size as well, which enabled us to count the number of slices of bread. Portions of fruits and vegetables were counted based on the guidelines from the Dutch Food Composition Database. For instance, two mandarins are classified as one portion of fruit and five cherry tomatoes as one portion of vegetables. Last, we counted the number of snacks, which were usually packed per portion. After processing the photographs, a second researcher checked congruence. When dissonance between interpretation of food groups or quantities occurred, a third researcher checked these photographs and disagreement was discussed until consensus was reached.

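### Adjusting at-school intake for at-home intake does not show whether children compensate at home; at-home intake has to be the outcome

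*Protocol article*

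**What the plan says.** Section 2.4.1 of the protocol article ties the question and the method together in one sentence. To find out whether school changes are offset at home, "we will adjust at-school child dietary behaviour for at-home child dietary behaviour". At-school intake stays the dependent variable and at-home intake is the covariate. The covariate is a "combined score of consumption in the morning and after school, derived from the parent and child questionnaire". Under section 2.3.1, questionnaires were completed at all three waves (T0, T1, T2), so at T1 and T2 the covariate is recorded after exposure has begun.

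Section 2.3.1 also gives at-home diet a status of its own: "Secondary outcome measures included dietary behaviour at home with regard to the products mentioned above". The sentence in section 2.4.1 that sets out the effect models does not carry this through. It names only at-school diet and determinants: "To analyse the effect of the intervention on the combined scores of at-school dietary behaviour and behavioural determinants, we will use multilevel regression analyses". Nowhere does the article say that at-home or total intake will be compared across waves to answer the compensation question. It also gives no rule for reading the adjusted result.

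**The concern.** Compensation means that the programme moves home intake in the direction opposite to school intake. It is an effect of exposure on home intake. A model with school intake as outcome and home intake as covariate estimates something else: the school difference between children whose home intake is the same. Because home intake may itself have been changed by the programme, holding it fixed removes from view the change that the analysis is meant to find.

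At stake is whether gains at school improve the child's diet overall or are cancelled at home. If the adjusted school effect persists, a reader could easily take that as reassurance, although the same result can arise when the benefit has been fully cancelled.

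**Working it through.** **Inputs.** The plan gives no figure for compensation. The effect size is borrowed from the sample-size paragraph of section 2.4.1: "d = 0.5, SD = 1.0, α = 0.05, power 80"%. (Those inputs give 2 × (1.96 + 0.84)² / 0.5² ≈ 63 per group, two-sided, and not the stated 107. That is a separate matter, and nothing below depends on it.) The at-home effect g and the correlation ρ are not in the document. They are assumptions, shown as ranges.

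**Model.** Take an item the programme aims to reduce, in SD units, with T = 0 at baseline and T = 1 at follow-up:

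- School: S = bT + e_S
- Home: H = gT + e_H
- Equal residual SDs, with correlation ρ between e_S and e_H within exposure groups

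Write e_S = ρe_H + u, with u unrelated to H and T, and substitute e_H = H − gT:

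S = (b − ρg)T + ρH + u

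The three candidate analyses therefore estimate:

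- S on T and H (planned): b − ρg
- H on T: g, the compensation itself
- S + H on T: b + g, the net effect

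**Planned coefficient with b = −0.5:**

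| ρ | No compensation (g = 0) | Half (g = +0.25) | Full (g = +0.5) |
|---|---|---|---|
| −0.3 | −0.50 | −0.425 | −0.35 |
| 0 | −0.50 | −0.50 | −0.50 |
| 0.3 | −0.50 | −0.575 | −0.65 |
| 0.5 | −0.50 | −0.625 | −0.75 |
| True net effect | −0.50 | −0.25 | 0 |

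For example, at ρ = 0.3 with full compensation: −0.5 − 0.3 × 0.5 = −0.65.

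At ρ = 0 the coefficient carries no information on g. At positive ρ, compensation makes the school effect look larger. At negative ρ it shrinks, but at ρ = −0.3 it is still far from the true net effect of 0.

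**Simulation check.** The set-up was 125 children per group (the article's 25 per class × 5 schools), 1,000 replicates, ordinary least squares without clustering, ρ = 0.3 and full compensation:

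| Model | Mean estimate | Replicates with p < 0.05 |
|---|---|---|
| S on T and H (planned) | −0.649 | 100% |
| H on T | +0.502 | 96.9% |
| S + H on T | 0.004 | 5.5% |

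With no compensation at the same ρ, the planned model gave −0.493 and was significant in 98.1% of replicates. Significance of the planned coefficient thus hardly separates the two situations, whereas the model for H does. Clustering is ignored here, so the detection rates are likely to be optimistic. The contrast between the models does not rest on them.

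**The case against.** **At-home diet is already a secondary outcome.** In this design a secondary outcome would ordinarily be compared across waves, and a condensed article may leave each model to a fuller plan. This stands in part: the data exist and such a model may be intended. But the article does not leave the compensation question open. It assigns that question to the adjustment, and its model sentence omits at-home diet.

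**The adjusted model is not wholly uninformative.** A reader might infer that it can never reveal compensation. That goes too far. When ρ is not 0, g can be recovered as (unadjusted − adjusted) / home coefficient; at ρ = 0.3 this is (−0.50 + 0.65) / 0.3 = 0.5. The article does not propose this step, which is only an indirect way of regressing home intake on exposure and fails at ρ = 0. The defect lies in the adjusted coefficient read alone.

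**The direction of distortion is unknown.** A reader might infer that full compensation always leaves the adjusted effect the same or larger. That fails for negative ρ, which cannot be excluded: children who take less of an item at school may take more at home. Stable preferences would push ρ the other way.

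**No misreading is written into the plan.** Taking a persisting effect as absence of compensation is a natural reading, but the article states no decision rule. The text supports a risk of misreading, not a certain wrong answer.

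**The algebra is linear.** Section 2.4.1 also provides for Poisson and logistic models, where b − ρg does not hold exactly and a school-plus-home sum has no simple meaning for a categorical outcome. This limits the formula and the total-intake remedy. It does not make conditioning on a post-exposure outcome a test of whether that outcome changed.

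**Conclusion.** The concern holds in a bounded form. As written, the analysis does not answer the plan's own question, because the adjusted at-school coefficient is neither the change at home nor the net change. With b = −0.5 SD, full compensation gives values from −0.35 (ρ = −0.3) to −0.75 (ρ = 0.5), against −0.50 with none. A persisting adjusted effect therefore cannot count as evidence that children do not compensate.

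The figures rest on a linear model, equal SDs, the plan's d = 0.5 and assumed values of ρ and g. That the adjusted coefficient is not g does not depend on those particular values.

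A reader might also infer that the main result is in doubt. The documents do not support that: the at-school effect models are specified without this adjustment and stand as they are. This is a supplementary analysis that should be corrected before it is run, not a flaw in the design or the main comparison.

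**What to change.** In section 2.4.1, replace the sentence on compensation with models that target it. Keep the same same-grade T1 and T2 versus T0 comparison and multilevel structure:

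- fit at-home intake of each food group as the outcome;
- for outcomes measured as amounts or counts, also fit total intake (at-school plus at-home, both from the questionnaires) as the outcome and report it as the net effect;
- for categorical outcomes, use the at-home model only.

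State that compensation will be judged from these models, that is, by whether home intake moves against the school change. Drop the adjusted at-school model, or keep it as descriptive only.

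The cost is a change of wording and up to two extra models per food group. The questionnaires already supply the data.
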